| * Cycle Length is 4 weeks, with treatment on Days 1 and 4 of Weeks 1 through 3; week 4 is a rest  week (no treatment)  ** The only pre-study data that will be used for data analyses are ECOG status, baseline CT or PET/CT, and LDH. See section 5.1.4 for details.  a: Pre-study requirements must be completed **within** **the following time**  **frames:**  Within **4** weeks: tumor assessments based on contrast CT of chest and abdomen or PET/CT;  Within **2** weeks: medical history, physical exam, vital signs, height, weight, ECOG, evaluation of symptoms and medications, clinical chemistry, hematology, LDH  Within **1** week: pregnancy test for women of childbearing potential  b: Specific chemistries are listed in section 5.2.2. Renal function will be assessed using the Cockcroft-Gault formula.  c: Serum pregnancy test for women of childbearing potential  d: These tests are performed with results available for review within 24 hours before administration of CPI-613  e: CPI-613 is given as a 2-hr IV infusion via a central venous catheter. Treatment with CPI-613 may be adjusted +/- 1 day.  f: Imaging performed while on treatment should be preferably obtained on day 3, 4, or 5 of week 4 during cycles 2, 4,  6 and every two cycles thereafter until progression.  g: Survival and post-study cancer treatment will be monitored bimonthly via telephone contact by the study PA after  patients are taken off of the trial. Phone contact will continue indefinitely.  h: Physical exam and clinical evaluation to be completed within 72 hours prior to treatment with CPI-613 | | | | | | | | | |

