### 5.1.3 Tumor Assessment

Tumor response will be assessed based on RR, and PFS, derived from contrast CT of chest and abdomen and/or PET/CT at baseline and after every two cycles. Contrast CT and/or PET/CT should be performed during week 4, preferably on Wednesday or later (days 3, 4 or 5). RR is the primary endpoint, whereas PFS and OS are secondary endpoints.

According to the Response Evaluation Criteria in Solid Tumors (RECIST), the efficacy of treatment for solid tumors is determined by the tumor size. RECIST criteria are the golden standard to evaluate the tumor. In this study RECIST criteria will be used to evaluate response. However, there is a *pseudoprogression* phenomenon described with the use of CPI-613 in Phase I solid tumor studies (Lee et al. 2012).

It is felt that if CPI-613-induces necrosis of the tumor lesion there may be some radiographic evidence for increasing size. CPI-613 induces tumor necrosis due to its mechanism of action – selectively targeting the altered form of mitochondrial energy metabolism in tumor cells, causing changes in mitochondrial enzyme activities and redox status, which leads to apoptosis, necrosis, and autophagy of tumor cells (Lee et al., 2011; Lee et al., 2012; Senzer et al., 2012; Zachar et al., 2011; Retter et al., 2012).

For the purposes of this study, pseudoprogression will be defined and considered in patients who meet RECIST criteria of progression. It will be the treating physician’s discretion to continue treatment in this situation if the patience is deemed to be getting clinical palliative benefit. In these patients, the study drug can be given for another two cycles prior to making definitive determination of progression or response.

OS will be determined from the first dose of CPI-613 to death, assessed until patient death..Post-study survival, medical and cancer treatment information will be collected bimonthly via telephone contact after treatment termination.

RR is defined as % of patients who experienced a complete response (CR) or partial response (PR). CR and PR are based on Response Evaluation Criteria in Solid Tumor (RECIST) Version 1.1 (Eisenhauer et al. 2009). The best response recorded from the start of the treatment until disease progression (DP) will be considered.

PFS will be determined from the first dose of CPI-613 to DP or death due to any cause.

*5.1.4 Use of pre-study data for analyses*

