## 6.2 Adverse Event-Related Dosing Delay and Dose Modification

For adverse events unrelated to serum creatinine elevation or reduction in renal function but are possibly related to CPI-613, the occurrence of Grade 1 toxicity does not generally require dose modification for subsequent doses for that patient. However, if Grade 2 toxicity (other than alopecia and nausea) probably related to CPI-613 develops, treatment is to be withheld and can resume only after the Grade 2 toxicity has been reduced to Grade 1 or below, and the dose level for subsequent doses for that patient will be reduced by 25% of the dose at which such Grade 2 toxicity occurs. Grade 2 alopecia and nausea do not require withholding treatment or dose reduction. If Grade 3 or 4 toxicity probably related to CPI-613 develops, dosing of CPI-613 of that patient will be withheld and the patient shall be monitored for recovery from, and reversibility of, such Grade 3 or 4 toxicity. To resume treatment with CPI-613 for a patient who has had CPI-613-related Grade 3 or 4 toxicity, the Grade 3 or 4 toxicity must be reduced to Grade 1 or below, and the dose level for subsequent doses for that patient will be reduced to 50% of the dose at which such Grade 3 or 4 toxicity occurs.

For adverse events related to creatinine elevation or reduction in renal function that are possibly related to CPI-613, dosing of the patient will be withheld if the severity level is Grade 1 or above. Treatment can resume only after the toxicity has been reduced to Grade 0. The dose level for subsequent doses for that patient will be reduced by 15% if the severity level is of Grade 1, by 25% for Grade 2 toxicity, and by 50% for Grade 3 or 4 toxicity.

Furthermore, if the toxicity possibly related to CPI-613 is acute renal failure and the severity level is Grade 3 or 4, further patient enrollment will be temporarily suspended in order to enable assessment of the following aspects of the trial and implementation of corrective measures or protocol amendment, and if necessary:

- compliance of the study sites and investigators to the study protocol

- evaluation of the appropriateness of the procedures for monitoring renal function

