# 9.0 STATISTICAL CONSIDERATIONS

This is a pilot study with the primary goal to be able to determine initial estimates of response rate (RR), and secondary goals to determine progression-free survival (PFS) and overall survival (OS). Data from this trial will also provide additional data concerning the safety profile of the CPI-613 therapy. We now describe anticipated accrual rates, proposed analyses, and sample size considerations.

Accrual Rate

We anticipate accruing one to two patients per month for this protocol. Thus, we anticipate that we will reach the target sample size of 20 patients treated at MTD within eighteen months.

Proposed Analyses

The analyses for this protocol will be primarily descriptive. With a sample size of 20 treated at MTD, we will be able to get initial estimates of RR, PFS, OS, and safety and toxicity.

For the primary outcome of tumor response rate we will present the proportion of patients who are CR, PR, SD or PD (Complete response, Partial response, stable disease and progressive disease, respectively). In addition, we will estimate the proportion of responders as the percent of patients who are SD, PR and CR, as well as RR (sum of PR + CR) and Disease Control Rate (DCR, which is the sum of SD, PR and CR). For these rates we will also include 95% confidence intervals.

For the time-to-event outcomes, we will estimate survival curves for OS and PFS using Kaplan-Meier techniques. In addition, we will estimate the 6 month and 1-year OS and PFS rates for these participants. We will estimate median overall and progression free survivals for these patients as well. We will also examine safety and toxicities for these 20 patients by looking at each toxicity identified earlier in the protocol by grade.

Sample Size Considerations

Since this is a single arm pilot study, our primary goal is to gather preliminary data on response rates and not to test a specific hypothesis per se. With this sample size we will be able to estimate the response rate using a 2-sided 95% confidence interval with an interval that will extend no more than 0.21 from the observed response rate (if we conservatively assume a response rate of 0.5 for calculations).

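### Scans are scheduled by cycle number and only on treatment, while dose holds are open-ended, so PFS ascertainment can depend on toxicity

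*Protocol*

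**What the plan says.** Footnote f to Table 5-1 (Section 5.0) reads "Imaging performed while on treatment should be preferably obtained on day 3, 4, or 5 of week 4 during cycles 2, 4", and continues with "6 and every two cycles thereafter until progression". Section 5.1.3 has response rate and PFS "derived from contrast CT of chest and abdomen and/or PET/CT at baseline and after every two cycles". The Schema gives the same timing. None of these places ties a scan to calendar time. The nominal cycle is fixed in the Table 5-1 notes: "Cycle Length is 4 weeks, with treatment on Days 1 and 4 of Weeks 1 through 3".

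Section 6.2 sets the holds. For Grade 2 non-renal toxicity other than alopecia and nausea, "treatment is to be withheld and can resume only after the Grade 2 toxicity has been reduced to Grade 1 or below". Grade 3 or 4 toxicity must fall to the same level. Renal events trigger a hold from Grade 1, and "Treatment can resume only after the toxicity has been reduced to Grade 0". No maximum duration is given, and the section does not say what happens to the cycle count or the scan date during a hold.

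In Table 5-1, imaging appears only pre-study and in week 4 of treatment cycles. The follow-up column contains telephone contact alone. The telephone form (Appendix E) asks about survival, later treatment and hospice care, with no item on progression. Section 6.3 asks for a final evaluation when treatment ends but does not name imaging.

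PFS is counted from the first dose (Section 5.1.3), and Section 9.0 states that "we will estimate the 6 month and 1-year OS and PFS rates for these participants".

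**The concern.** PFS is a calendar-time endpoint, but the scans that detect progression follow a treatment clock. Progression seen on imaging is dated at the scan that shows it. If a hold stops that clock, a patient with toxicity is scanned later than one without, and the 6-month and 1-year rates then partly reflect tolerability. A patient on a prolonged hold may not reach week 4 of the next even cycle. One who stops for toxicity before progressing leaves the imaging schedule altogether. In both cases progression could go unseen until death. This is a matter of visit scheduling, and no later analysis can recover scans that were not taken.

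**Working it through.** The protocol gives no figure on this point, so the check starts from its nominal scan days.

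**Step 1. Scan days without holds.** Inputs from Table 5-1: a 28-day cycle, with scans on day 3, 4 or 5 of week 4 in even cycles. Scan day = 28 × (cycle − 1) + 21 + (3 to 5).

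- Cycle 2 (scan 1): 28 + 21 + 3 to 5 = days 52-54
- Cycle 4 (scan 2): 84 + 21 + 3 to 5 = days 108-110
- Cycle 6 (scan 3): 140 + 21 + 3 to 5 = days 164-166
- Cycle 12: 308 + 21 + 3 to 5 = days 332-334

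**Step 2. Slack to the landmarks.** Six months is 365.25 / 2 = day 182.6. The slack after the cycle 6 scan is 182.6 − 166 = 16.6 to 182.6 − 164 = 18.6 days. For the 1-year rate it is 365.25 − 334 = 31.3 to 365.25 − 332 = 33.3 days.

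**Step 3. Recorded 6-month PFS in a held patient.** The protocol gives no hold lengths and no time to progression. Assumed here: the hold pauses the cycle, it falls before scan 2, progression is exponential with a median of 2 or 3 months (60.9 or 91.3 days), and nobody dies. A patient then counts as progression-free at 6 months if no progression has occurred by the last scan before day 182.6. The probability is S(t) = 2^(−t/median), with t the day of that scan (mid-window).

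| Hold | Deciding scan | Median 2 months | Median 3 months |
|---|---|---|---|
| none | scan 3, day 165 | 15.3% | 28.6% |
| 10 days | scan 3, day 175 | 13.6% | 26.5% |
| 16 days | scan 3, day 181 | 12.7% | 25.3% |
| 20 days | scan 2, day 129 | 23.0% | 37.6% |
| 28 days | scan 2, day 137 | 21.0% | 35.3% |
| 42 days | scan 2, day 151 | 17.9% | 31.8% |
| true value | day 182.6 | 12.5% | 25.0% |

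A 20-day hold raises the recorded rate by 23.0 − 15.3 = 7.7 or 37.6 − 28.6 = 9.0 points. A hold shorter than the slack lowers it, towards the true value. Beyond the threshold, the excess shrinks as a hold before scan 2 lengthens.

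**Step 4. Whole-trial size.** If 25% of patients were held this way (an assumption), the effect is 0.25 × 7.7 to 0.25 × 9.0, about 2 points. One patient of 20 is 5 points. The Wald 95% half-width is 1.96 × √(0.153 × 0.847 / 20) = 16 points, or 1.96 × √(0.286 × 0.714 / 20) = 20 points.

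**Step 5. Allowing for deaths.** A simulation of 400,000 patients per setting used exponential progression (median 6, 10 or 14 weeks), then exponential survival with median 19.5 weeks minus the progression median. The 19.5 weeks is the middle of the 4 to 5 months in Section 1.1. Scans were at week 7.5 and every 8 weeks, against the same grid delayed by 2-6 weeks in 10-40% of patients.

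- Mean recorded PFS was 0.2-2.2 weeks longer in held patients and 0.02-0.9 weeks longer overall.
- The median moved both ways. It rose from 7.5 to between 9.5 and 13.5 weeks (progression median 6 weeks, 25-40% held). It fell from 15.5 to between 13.5 and 14.6 weeks (10 weeks, 40% held for 4-6 weeks).

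**Step 6. Patients who stop for toxicity.** In the same model, patients stopped within the first 8 weeks, had no further scan and counted only at death. Recorded PFS in them was 5-15 weeks longer on average. With 10-30% stopping this way, the overall mean rose by 0.5-4.5 weeks and the 6-month rate by 1-11 points.

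**The case against.** The strongest reply is that the delay is assumed. The cycle is defined as four weeks, and Section 6.2 withholds dosing without saying that the cycle pauses. If held doses are skipped inside a fixed cycle, no scan moves. That stands as one reading, but the section's own title speaks of dosing delay and nothing decides between the two, so sites could act differently.

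A reader might infer that toxicity always delays scans and always inflates PFS. The documents do not support this. The delay depends on the unsettled reading, short holds pull the 6-month figure towards the truth, and the median can fall.

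A reader might also infer that a patient who never recovers gets no further scan and has no way off an indefinite hold. Section 6.3 offers several exits: unacceptable toxicity, ineligibility for further treatment, and investigator's discretion. Each leads to a final evaluation and telephone follow-up. That evaluation might include a scan, and footnote f's end point of progression could be read as continuing imaging. The text supports only that no further scan is scheduled.

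Finally, PFS is secondary, the analysis is descriptive with no hypothesis test, and no distortion of the primary response rate has been shown. All of that stands and limits the weight of the point.

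**Conclusion.** The point holds in a limited form. Scan dates are tied to cycles and to being on treatment, holds have no stated limit, and the protocol leaves open whether a hold pauses the cycle. PFS ascertainment can therefore depend on toxicity. The 8-9 point excess in 6-month PFS applies to held patients only. It rests on a paused cycle, a 20-day hold before scan 2, exponential progression and no deaths. The gap after early stopping can matter more per affected patient, but its 5-15 weeks assume that no imaging is done and that the event is counted at death. Hold rates, hold lengths and progression times are all assumed. In a 20-patient descriptive pilot the impact is modest, and the remedy is cheap.

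**What to change.** In Table 5-1 footnote f, Section 5.1.3 and the Schema:

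- Count scans in calendar time from the first dose: the current days 52-54, then every 8 weeks. For a patient without delays this keeps the rest-week timing, before the next treatment period.
- State that holds, delays and missed doses do not move the scans.
- Continue the same schedule until progression in patients who stop treatment before progressing.
- Keep imaging through any additional cycles that Section 5.1.3 allows after RECIST progression.

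Have the Measurement Form (Appendix G) record days or weeks from first dose as well as cycle. Reconcile footnote f with Section 6.2 on whether a hold pauses the cycle. No hold limit or dosing rule is proposed.

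The cost is a wording change and a scheduling instruction. Patients without delays have no added scans on treatment. A held patient may be scanned after fewer doses than planned, and patients who stop early for reasons other than progression will have some further scans.

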### 5.1.2 Safety Assessment

The safety of CPI-613 will be assessed from the first dose to 1 month after last dose of CPI-613. The assessment will be based on:

- evaluation of symptoms

- vital signs

- ECOG performance status and survival

- clinical chemistry

- renal function

- hematology

The specifics of the safety tests are described in Section 5.2. All safety assessment tests are performed during screening (performed within 2 weeks prior to Cycle 1 treatment with CPI-613. Symptom evaluation and vital signs should be performed prior to each administration of CPI-613. ECOG performance status, clinical chemistries, renal function, and hematology should be performed on day 1 of weeks 1, 2, and 3 for each treatment cycle, with results available for review within 24 hours before administration on day 1 of study drug administration.

###

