## 6.1 Sample Size, Dose Levels and Justification of the Dose

The sample size will be 20 for this pilot trial.

This study will use the maximum tolerated dose (MTD) established in the study conducted by Pardee and colleagues (CCCWFU 29109; IRB00012124). This MTD for single-agent use of CPI-613 infused over 2 hours is 3,000 mg/m^2^.

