## 6.3 Duration of Treatment for Each Patient at Each Cohort

Six months of treatment is recommended for patients who have a response, unless or until:

- Patients exhibit progression of disease together with worsening of biliary function, no longer meeting eligibility criteria, or exhibiting symptomatic progression; or patients exhibit progression of disease which was confirmed after 2 additional treatment cycles

- Unacceptable toxicity from CPI-613

- Patient withdrawal of consent

- Investigator’s discretion to withdraw patients from the study because continued participation in the study is not in the patient’s best interest.

- Undercurrent illness: a condition, injury, or disease unrelated to the intended disease for which the study is investigating, that renders continuing the treatment unsafe or regular follow-up impossible

- General or specific changes in the patient's condition that renders the patient ineligible for further investigational treatment

- Non-compliance with investigational treatment, protocol-required evaluations or follow-up visits

- Termination of the clinical trial by the sponsor

However, if therapy is considered beneficial according to the opinion of the treating physician, additional cycles of therapy may be given on the same treatment plan indefinitely up to the time of clear disease progression.

When terminating treatment during this trial, the investigator should make every effort to contact the patient and to perform a final evaluation. Also, the reason(s) for withdrawal from the study must be recorded.

Survival and post-study cancer treatment will be monitored via bi-monthly telephone contact once patients are removed from trial. All patients will be followed until death.

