**What was the result of the telephone call?**

Call was unanswered

Spoke directly with the subject

Spoke to a family member

Left a message

Comments: ________________________________________________________________________________________________________________________________________________________

**Is this subject still living?** Yes  No  Unknown

**If the subject has expired, list date of death:** ____ / ____ / ____

**Is the subject currently receiving or has received since coming off the 62113 trial systemic chemotherapeutic cancer treatment?** Yes  No  Unknown

Type of cancer treatment being received (including the dose, dosing schedule and duration, if applicable and if known): _________________________________________________________________________

**Is the subject receiving radiation for cancer treatment?** Yes  No  Unknown

Type of radiation treatment being received: _________________________________________________________________________

**Is the subject receiving palliative / Hospice care?** Yes  No  Unknown

If yes, date of enrollment into Hospice: ___ ___ / ___ ___ / ___ ___

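### The one-month safety window has no scheduled assessment after treatment stops, and progression is not systematically captured off treatment, although PFS depends on it

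*Protocol*

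**What the plan says.** **Safety.** Protocol Section 5.1.2 states: "The safety of CPI-613 will be assessed from the first dose to 1 month after last dose of CPI-613". It bases this on symptoms, vital signs, ECOG status and survival, chemistry, renal function and hematology. It then ties those tests to screening and to dosing days.

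**Progression.** Section 5.1.3 defines the endpoint: "PFS will be determined from the first dose of CPI-613 to DP or death due to any cause". Section 9.0 promises more than a median: "we will estimate the 6 month and 1-year OS and PFS rates for these participants". Table 5-1 footnote f places the scans in even-numbered cycles: "Imaging performed while on treatment should be preferably obtained on day 3, 4, or 5 of week 4".

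**After treatment.** Section 6.3 lists several reasons to stop that are not progression: toxicity, withdrawal of consent, another illness, non-compliance and investigator discretion. It also recommends six months of treatment for responders. It asks for an effort to make a final evaluation at termination, without content or timing. Then: "Survival and post-study cancer treatment will be monitored via bi-monthly telephone contact once patients are removed from trial". The form for that call is Appendix E. It records vital status and date of death, hospice care, radiation, and later chemotherapy ("Is the subject currently receiving or has received since coming off the 62113 trial systemic chemotherapeutic cancer treatment"), plus free comments.

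**The concern.** Two outcomes are defined over a period in which the schedule makes no provision to observe them.

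Safety and toxicity are secondary outcomes (Section 2.2). Events that appear after the last dose would be recorded only if someone happened to learn of them. The resulting safety profile could look more favourable than it is, with nothing in the data to show how much was missed.

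PFS is also a secondary outcome. For a patient who stops without progression, no further scan is scheduled and no call asks about progression. The analyst is left with two choices. One is to wait for death, which counts time after an unrecorded progression, possibly on another therapy, as progression-free. The other is to censor at the last scan, which assumes that stopping is unrelated to prognosis. A statistical analysis plan can choose between these, but it cannot supply progression data that the schedule and forms never ask for.

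**Working it through.** The protocol gives no figure on this point. Its one design calculation concerns the precision of the response rate and plays no part here. The check is a comparison of sections, followed by an illustration of direction.

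**Step 1. What falls in the safety window.** Count days within a patient's last cycle.

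| Item | Source | Day of cycle |
|---|---|---|
| Adverse event evaluation | Table 5-1 | 1 |
| Chemistry and hematology, before dosing | Table 5-1, footnote d | 1, 8, 15 |
| Last dose, week 3 day 4 | Section 6.0 | 14 + 4 = 18 |
| Scan, even cycles only | Footnote f | 21 + 3 = 24 to 21 + 5 = 26 |
| Next adverse event evaluation | Table 5-1 | 29 (next cycle, day 1) |

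The day 29 evaluation would come 29 − 18 = 11 days after the last dose, but it does not take place for a patient who has stopped. The last laboratory test precedes the day 15 dose, so the doses on days 15 and 18 have no scheduled laboratory test after them. In an even cycle one scan falls 6 to 8 days after the last dose. Nothing else is scheduled within the month. If bimonthly means every two months, the first call comes after the window closes. If it means twice a month, calls fall inside the window, but the form still has no adverse event item.

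**Step 2. What is known about progression off treatment.** The follow-up column of Table 5-1 holds only the phone contact. Appendix E has no progression item. It asks for the duration of later treatment, if known, but not its start date.

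**Step 3. Direction of the effect on PFS if death is the event after stopping.** Assume independent, constant hazards. Median survival is M = 4.5 months, the midpoint of the 4 to 5 months in Section 1.1. Median time to progression T and the share s who stop unprogressed are assumptions; the protocol gives neither.

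- Hazards: a = ln 2 / T, d = ln 2 / M, and stopping c = (a + d)·s / (1 − s).
- PFS with progression fully observed: exp(−(a + d)t).
- PFS read literally: exp(−dt)·[exp(−(a + c)t) + (c / (a + c))·(1 − exp(−(a + c)t))].

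For T = 2, s = 0.20 and t = 6: a = 0.347, d = 0.154, c = 0.501 × 0.25 = 0.125.

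- Fully observed: exp(−0.501 × 6) = 0.050.
- Literal: exp(−0.924) × [exp(−2.830) + 0.265 × (1 − exp(−2.830))] = 0.397 × (0.059 + 0.250) = 0.122.

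| Assumed T (months) | Fully observed 6-month PFS | Literal, s = 10% | Literal, s = 20% | Literal, s = 40% |
|---|---|---|---|---|
| 1.5 | 2% | 7% | 11% | 19% |
| 2 | 5% | 9% | 12% | 20% |
| 3 | 10% | 13% | 16% | 22% |

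With progression dated at 8-weekly scans, T = 2 and median survival 4.8 months, a simulation gives about 6% rising to 13% (20% dated at death) and 17% (30%).

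In the trial itself, "The sample size will be 20 for this pilot trial". A move from 5.0% to 12.2% is therefore 20 × 0.050 = 1.0 against 20 × 0.122 = 2.4 patients.

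**Step 4. Why no median is quoted.** With 8-weekly scans the median tends to sit on the first scan date, 56 days or 1.84 months. Whether it stays there or jumps depends on whether just over or just under half the patients have events by that scan, and on the assumed link between progression and death. The result reflects the model more than the protocol.

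**The case against.** A reader might infer that nothing is collected after the last dose. The protocol does not support that. Section 6.3 asks for a final evaluation. Section 6.2 requires patients with Grade 3 or 4 toxicity probably related to CPI-613 to be monitored for recovery. Section 8.1 requires all adverse events to be logged and sets no end date. Section 5.1.3 says the calls also gather medical information. Appendix F treats follow-up in the medical record as a study component that can outlast dosing. Deaths are captured. This all stands, so the gap lies in what is scheduled and asked. None of these provisions sets a contact at one month or puts an adverse event or progression item on the call form. The log in Appendix C itself says that only Grade 3 or higher needs recording.

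A reader might also infer that PFS simply becomes overall survival for these patients. That follows only from the literal definition. Appendices D and G date every scan, so an analysis plan, which is not at hand, can censor at the last one. The absence of a censoring rule from the protocol is no fault. What remains is that stopping for toxicity or decline is unlikely to be unrelated to prognosis.

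Nor is the number affected necessarily large. Section 6.3 allows cycles to continue up to clear progression where the physician judges them beneficial, which keeps such patients on scheduled imaging. PFS is a secondary, descriptive endpoint without a hypothesis test. The primary endpoint, response rate, comes from on-treatment scans and is little touched.

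**Conclusion.** The point holds as a mismatch between the stated outcomes and the schedule and forms meant to deliver them. Table 5-1 and Appendix E do not deliver the safety window of Section 5.1.2. They also do not systematically capture progression in patients who stop without it.

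The safety half needs no assumption beyond reading bimonthly as every two months, and under the other reading the form still omits adverse events. For PFS, the upward direction under the literal definition holds in every scenario above. Its size does not carry over to this trial, because both the stopping share and the time to progression are assumed. Under censoring at the last scan the bias could go either way and cannot be sized from the protocol.

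The change should be made because it is cheap and because data not requested during follow-up are hard to recover later. It does not put the primary analysis in doubt.

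**What to change.** - Time the first follow-up call at about 30 days after the last dose, and show it in Table 5-1 as the end of the safety window. State what bimonthly means for the later calls.
- Add to Appendix E: adverse events since last contact; progression since last contact (yes or no, date, and whether by scan or clinically); and the start date of any new anti-cancer treatment.
- For patients off treatment without progression, record the results of routine-care scans until progression or new therapy. State how new therapy is handled when PFS is reported.
- Reconcile Table 5-1 and its footnotes with Sections 5.1.2, 5.1.3 and 6.3 and Appendix E, so that the stated windows and the scheduled contacts agree.

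The cost is a few form fields, one re-timed call and some abstraction from the medical record. No procedures are added and no treatment rule changes. Routine-care scans will be irregular in timing, so progression dates off treatment will be less exact than those on treatment, and the report should say so.
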